**Methods:**

We will perform a parallel randomized controlled trial. PwMS who are followed by general private-practice neurologists will be randomly assigned to the intervention group (NP-led care) or the ‘usual care’ control group (general neurologist or family physician and registered nurse support). In the intervention group, the NP will assess and provide care to the MS patient and their caregiver at a baseline visit, with 3-month and 6-month follow-up visits. PwMS in the control group will receive usual care provided by their community neurologists or family physicians with the standard assistance provided by registered nurses experienced in MS care. The primary outcome will be the difference in change in the patient’s anxiety and depression scores as measured by the validated Hospital Anxiety and Depression Scale (HADS) questionnaire at 3 months. Secondary outcomes will include difference in change in HADS at 6 months; Modified Fatigue Impact Scale scores (MSIF) at 3 and 6 months; EQ-5D scores at 3 and 6 months; caregiver health-related quality of life in MS measures (CAREQOL-MS) at 3 and 6 months; number of visits and phone calls to healthcare professionals recorded by patient, and satisfaction with NP-led care vs usual care measured by the validated Consultant Satisfaction Questionnaire.

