### Statistical analysis

Data analysis will be performed using the computer R 3.4.0 software (Vienna, Austria; https://www.R-project.org/) and SAS 9.4 software (SAS Institute Inc. Cary, NC, USA). Patient demographic and clinical characteristics will be analysed using descriptive statistics.

The primary outcome of difference in change of HADS-D and HADS-A from baseline to 3 months between the intervention and control, will be tested using an independent *T*-test. The last observation will be carried forward in the case of missing data. Secondary outcomes will be analysed using the same methods as described below. The CSQ will be treated as continuous variables with an overall satisfaction score as a sum of the sub-scales for each question in the CSQ.

Categorical variables will be reported using frequency and percentage and continuous variables will be reported using mean (SD) or median [interquartile range (IQR)] as appropriate. Univariable analysis will be conducted to determine if there is a statistical significance between the outcomes (e.g. baseline to 3 months and 6 months, respectively). Chi-square and independent *T*-tests will be used for the univariate analysis, or where appropriate the non-parametric tests (Fishers test and Wilcoxon rank test). ANOVA and generalized linear models will be used to test for overall differences between the intervention and control at the different timepoints and variances amongst the variables by group and timepoints. Post hoc Tukey HSD (Honestly Significant Difference) test will be performed afterwards with adjustments made using the Bonferroni method. All test assumptions will be checked during the data analysis process. Statistical significance will be set at *p* values less than 0.05. In the case of missing data, we will utilize the last value carried forward method to impute missing values.

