### Data monitoring

There will be an interim analysis completed after the 3-month follow-up has been completed. The study involves PwMS completing validated surveys of their depression and anxiety scores which will be reviewed routinely by the NP and neurologist. If a PwMS depression and anxiety score falls drastically, the NP or neurologist will follow up with the patient and provide any necessary care or referral. Quality assurance of the data will be performed by the data entry researcher and the project manager for the trial. Any and all amendments will be communicated to all investigators, research ethics office, and the participants. The study investigators will make the final decision to terminate the trial if needed. Since this a smaller, single-centre study, we do not have plans for independent audit of trial conduct.

Electronic data will be collected and stored using the RedCap secure website which is housed behind the Faculty of Medicine and Dentistry firewall and secure server. Paper copies will be kept in locked cabinets within the EPICORE Centre as according to their standard operating procedures. Participants will be sent a reminder by the EPICORE Centre team to complete the questionnaires at baseline, 3 months, 6 months, and at 12 months to encourage participants to complete follow-up visits. The first or last observation will be carried through to account for any missing data during the data analysis.

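### Carry-forward and score-type tests cover diary counts of visits and calls with no use of observed time; the effect is modest and depends on diary coverage differing by arm

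*Protocol article*

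**What the plan says.** The abstract lists among the secondary outcomes the "number of visits and phone calls to healthcare professionals recorded by patient". The Outcomes section repeats this as a diary of outpatient contacts and adds emergency visits and admissions from a provincial database.

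The Statistical analysis section gives one rule for all secondary outcomes: "Secondary outcomes will be analysed using the same methods as described below". Only the satisfaction questionnaire gets a sentence of its own. The methods that follow are:

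- Two-group tests: "Chi-square and independent *T*-tests will be used for the univariate analysis, or where appropriate the non-parametric tests (Fishers test and Wilcoxon rank test").
- Models: "ANOVA and generalized linear models will be used to test for overall differences between the intervention and control at the different timepoints". No family, link, offset or exposure time is given.
- A general safeguard: "All test assumptions will be checked during the data analysis process".
- Missing data: "In the case of missing data, we will utilize the last value carried forward method to impute missing values". The Data monitoring section words this differently: "The first or last observation will be carried through to account for any missing data during the data analysis".

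On collection, the Data collection section has diaries submitted at the questionnaire time points. The Control arm section has usual-care diaries collected by the NP once the participant has finished the study. Emergency visits and admissions are searched in the database for the 6-month study period. The Drop-out criteria section allows withdrawal at any time.

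**The concern.** A questionnaire score describes a state at one moment. A visit count accumulates over an interval and means little without the length of that interval. Carrying a score forward at least yields a value on the right scale. Carrying a count forward does one of two things. If diaries are counted per interval, it enters one interval's contacts as the contacts of another interval that nobody observed. If they are running totals, it lets a partial total stand as the full one. Neither a t-test nor a rank test on the result knows how much time each person contributed.

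The third study objective is to compare outpatient visits and calls. The Outcomes section uses these counts to see whether the NP lowers the cost of other providers, and results go to the health service that will consider continued funding. If diary coverage differs by arm, the comparison mixes use of care with completeness of recording. Thinner recording in usual care would hide a reduction; thinner recording in the NP arm would create one. Uneven coverage is plausible. A control participant who leaves early, or declines the later NP visit, may never hand in a diary, whereas the NP arm has scheduled NP contacts at 3 and 6 months.

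**Working it through.** **The plan's own figures.** The protocol has no planning figure for any count. Its sample size (200, inflated to 220) is for a 1.5-point HADS difference. The only figure bearing on loss is the inflation: 1 − 200/220 = 9.1% overall, with no split by arm.

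**Assumptions (not in the documents).** Contacts are gamma-Poisson with mean 8 per 6 months, dispersion 0.7 and a constant rate within person. There are 110 per arm (220/2). People with incomplete follow-up are observed for a fraction T of the 6 months, uniform on 0.05 to 1. Carry-forward is read as using the first 3-month count for the second 3 months.

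**Expected bias by hand, 20% loss in usual care and 5% in the NP arm.**

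1. Raw counts. Mean T among those lost = (0.05 + 1)/2 = 0.525.
   - Usual care: 0.80 + 0.20 × 0.525 = 0.905.
   - NP arm: 0.95 + 0.05 × 0.525 = 0.976.
   - Bias factor: 0.976/0.905 = 1.08.
2. Carry-forward. Mean observed part of the first half among those lost = [(0.5² − 0.05²)/2 + 0.5 × 0.5]/0.95 = 0.393; doubled, 0.787.
   - Usual care: 0.80 + 0.20 × 0.787 = 0.957.
   - NP arm: 0.95 + 0.05 × 0.787 = 0.989.
   - Bias factor: 0.989/0.957 = 1.03.
   - All of this residual comes from people lost before 3 months, whose partial count is doubled as if complete.
3. At a true ratio of 0.75 these factors give 0.75 × 1.08 = 0.81 (raw) and 0.75 × 1.03 = 0.77 (carry-forward).

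**Simulation, 1500 trials per scenario.** NB is negative binomial with log observed time as offset, dispersion taken as known. The Wilcoxon test was run on raw counts only.

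True ratio 1.00 (estimated ratio; type I error):

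| Loss, usual care v NP | Raw ratio | Carry-forward ratio | NB ratio | t raw | Wilcoxon raw | t carry-forward | NB |
|---|---|---|---|---|---|---|---|
| 9% v 9% | 0.995 | 0.994 | 0.995 | 4.9% | 5.1% | 4.7% | 5.2% |
| 20% v 5% | 1.08 | 1.03 | 1.00 | 9.3% | 11.0% | 5.3% | 4.9% |
| 30% v 10% | 1.12 | 1.05 | 1.01 | 11.7% | 15.3% | 5.7% | 4.7% |

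True ratio 0.75 (power):

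| Loss, usual care v NP | t raw | Wilcoxon raw | t carry-forward | NB |
|---|---|---|---|---|
| none | 64.5% | 54.6% | 64.5% | 65.1% |
| 9% v 9% | 61.1% | 51.0% | 61.9% | 64.5% |
| 20% v 5% | 35.6% | 22.8% | 50.4% | 62.1% |

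The simulated ratios agree with the hand calculation. Against NB, the raw t-test loses 0.6 points with no loss and 3.4 with equal loss; the Wilcoxon loses 10.5 and 13.5. At 20% v 5% the carry-forward t-test loses 62.1 − 50.4 = 11.7 points and the raw t-test 26.5. Simulation error on a power near 50% is about √(0.25/1500) = 1.3 points.

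**Rare events** (mean 0.4, dispersion 1.5, true ratio 0.75, no loss): t 16.8%, Wilcoxon 14.9%, NB 17.0%. For emergency visits and admissions the choice of test matters little.

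**The case against.** Four points can fairly be made for the plan.

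- **Generalized linear models are named, and assumptions will be checked.** Poisson and negative binomial models belong to that class, and the family and offset for a secondary outcome without its own power calculation can be left to a SAP. This stands as far as the missing detail goes. It does not rescue the carry-forward rule, which is stated without exception: a count model fitted to carried-forward totals would still use invented contacts.
- **Unequal loss is assumed.** This stands. A reader might infer that the contact comparison will be biased. The documents do not support that, because no section reports or predicts loss by arm. At equal 9% loss, the case nearest the protocol's own allowance, the ratio is 0.995.
- **The largest losses belong to an analysis that is not planned.** This stands. The 8% bias, the type I error of 9% to 11% and the t-test power of 36% at 20% v 5% loss describe raw partial counts. With the planned carry-forward, on the reading used here, bias is about 3% and type I error 5.3%.
- **Database events do not depend on diaries.** This stands. A reader might extend the follow-up argument to emergency visits and admissions, but they are searched over a 6-month window and should be almost evenly observed unless withdrawal ends the search.

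An offset is also no cure for a diary that is never returned. Such a participant has no covered days and leaves the model.

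**Conclusion.** The point holds in a limited form. The protocol fixes carry-forward for every secondary outcome, and for diary counts that rule produces a wrong kind of value. Nothing in the protocol brings in observed time.

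The consequence is modest and conditional. If coverage differs by arm (20% v 5% assumed), the contact ratio shifts by about 3% with carry-forward, and power at a true ratio of 0.75 is 50% against 62%. With equal or complete follow-up there is no bias and the t-test is nearly as good as the count model; only the Wilcoxon fallback then gives up about 10 to 13 points.

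These sizes rest on the assumed mean, dispersion, constant rate, loss pattern and reading of carry-forward. The known dispersion slightly favours the negative binomial model. The outcome is secondary and has no sample size of its own, so this is a worthwhile improvement and no threat to the trial's main conclusion.

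**What to change.** 1. State that carry-forward, in either wording, does not apply to counts.
2. Analyse diary visits and calls by negative binomial regression on arm, with log(days covered by returned diaries) as offset. Report the rate ratio with its 95% CI.
3. Use the same count model for emergency visits and admissions over the fixed 6-month window.
4. Report by arm how many participants returned no diary, since the offset cannot correct for these.

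The cost is a slightly more complex model and the work of deriving the days each diary covers. The Trial status section places the final analysis still ahead, so the rest is a change of wording.

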PwMS will be included at baseline irrespective of whether they have depression at study entry, or long-term depression, or depression already managed with pharmacotherapy or therapies. This is because of studies suggesting that PwMS scoring high on depression levels often have not been previously identified as having depression or anxiety within a cohort [28], and that even those with previously identified depression or anxiety are often undertreated [45]. Baseline testing will be done for all participants; therefore, participants will become their own controls, as to outcomes on change in levels of depression and anxiety over 3 months, and then 6 months in addition to other quality of life outcomes. Therefore, we will see if the NP involvement and the consequent additional supports, counseling, etc., provides a change over time from baseline depression and anxiety levels. We postulate that depression and anxiety may be most responsive to the holistic approach of an NP over the short term in comparison with other quality of life measures [30, 47]. The primary outcome of depression and anxiety score changes at 3 months was chosen as the primary outcome due to published studies examining efficacy of interventions for depression and anxiety for PwMS carrying out active intervention strategies ranging in duration from 6 to 16 weeks (median 12 weeks), demonstrating overall efficacy in mainly depression and suggested efficacy in anxiety by a systematic review and meta-analysis [47].

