### Data collection

Participants may withdraw from the study at any time without effect to their care. They will be informed they will not receive any incentive for participation and the risks are not beyond the day-to-day risks. After the participants have provided informed consent, they will be invited to complete the questionnaires. PwMS will be asked to complete the Hospital Anxiety and Depression Scale (HADS) [74], Euro Quality of Life Measurement (EQ5D) [23], Modified Fatigue Impact Scale (MSIF) [81, 82], at specific timepoints (baseline, 3 months, 6 months, and 12 months); their caregivers (where applicable) will be asked to complete the Caregiver Health-Related Quality of Life in MS (CAREQOL-MS) questionnaire at the same timepoints [83]. These questionnaires will take approximately 10 to 15 min to complete at each time point. Participants will be asked to keep a participant diary submitted at the same time points, recording the number of outpatient visits and phone calls to their neurologists, family physicians, registered nurses, pharmacists, physiotherapists, occupational therapists, and other allied health professionals (such as massage therapists, chiropractors, dieticians). Alberta has a linked provincial system where all emergency visits and inpatient admissions are recorded. This database will be searched for any emergency visits and inpatient admissions for the 6-month period that the participants are involved in the study.

Participants’ satisfaction with the level of care provided to them will be measured at 6 months at the conclusion of their NP care using the validated Consultant Satisfaction Questionnaire (CSQ) [73, 84]. The CSQ consists of 18 Likert scale questions, ranging from 1 = strongly disagree to 5 = strongly agree, with the higher score indicating a higher level of patient satisfaction.

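### The group-by-timepoint ANOVA/GLM and Tukey step names no within-person term for scales repeated on the same people; the primary t-test on change is unaffected

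*Protocol article*

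**What the plan says.** In the protocol article, Data collection has participants complete HADS, EQ5D and MFIS "at specific timepoints (baseline, 3 months, 6 months, and 12 months". Caregivers complete CAREQOL-MS on the same schedule. The population section explains the design by saying that "participants will become their own controls".

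The Statistical analysis section then names three layers of analysis:

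- For the primary outcome, the change in HADS-D and HADS-A from baseline to 3 months "between the intervention and control, will be tested using an independent *T*-test".
- For a univariable layer: "Univariable analysis will be conducted to determine if there is a statistical significance between the outcomes (e.g. baseline to 3 months and 6 months, respectively". The tests follow: "Chi-square and independent *T*-tests will be used for the univariate analysis", with Fisher and Wilcoxon rank tests as fallbacks.
- For an across-time layer: "ANOVA and generalized linear models will be used to test for overall differences between the intervention and control at the different timepoints". The same sentence refers to variation by group and timepoint. Tukey HSD with a Bonferroni adjustment comes next.

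No paired test, repeated-measures ANOVA, mixed model, GEE or subject effect is named anywhere in the article. A general sentence promises that test assumptions will be checked, but gives no alternative for dependent observations.

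**The concern.** Ordinary ANOVA, generalized linear models and Tukey HSD all assume independent observations. Here the dependence is known from the design, because one person supplies two to four values per scale. If rows are pooled, the error variance mixes variation between people with variation within people, and it is wrong for both kinds of question:

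- The overall arm effect compares people, so pooling overstates the effective sample and false positives rise.
- The arm-by-time effect compares each person with themselves, so pooling discards the precision that the own-control design was meant to supply. Real effects are then missed.

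Two features of the plan add to this. If baseline counts as one of the timepoints, the overall arm effect is averaged with a visit at which randomization makes the expected difference zero. Carrying the last value forward copies earlier values into later rows, which a pooled analysis would count as new independent data.

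At stake are the secondary conclusions drawn from this across-time step for HADS, EQ5D, MFIS and CAREQOL-MS.

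**Working it through.** **Inputs from the article (Sample size and power analysis).** There are 100 participants per arm, the target difference is 1.5 points, power is 80% and two-sided alpha is 0.05.

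**Assumptions.** The article gives no within-person correlation ρ. I use 0.3 to 0.8, equal between all visits. It gives no SD either, so I back-solve one from the stated sample size.

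**Plan's own figure.** SD = 1.5 × √(100/2) / (1.960 + 0.842) = 1.5 × 7.071 / 2.802 = 3.79. In the other direction, an SD of 3.78 gives 100 per arm, or 200 in total. The stated size is therefore internally possible, but it cannot be reproduced without the SD.

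**Overall arm test on pooled rows.** With k visits, the true variance of the arm difference is the pooled-row variance times 1 + (k − 1)ρ. The actual size of the nominal 5% test is therefore 2 × [1 − Φ(1.96 / √(1 + (k − 1)ρ))]. At ρ = 0.5:

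- k = 2: 1.96/√1.5 = 1.600, size 11.0%
- k = 3: 1.96/√2.0 = 1.386, size 16.6%
- k = 4: 1.96/√2.5 = 1.240, size 21.5%

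**Within-person contrast on pooled rows.** The true variance is the pooled-row variance times (1 − ρ), so the size is 2 × [1 − Φ(1.96 / √(1 − ρ))].

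| ρ | Arm: months 3, 6 | Arm: baseline, 3, 6 | Arm: all four | Two-visit within-person contrast |
|---|---|---|---|---|
| 0.3 | 8.6% | 12.1% | 15.5% | 1.9% |
| 0.5 | 11.0% | 16.6% | 21.5% | 0.6% |
| 0.7 | 13.3% | 20.6% | 26.6% | 0.03% |
| 0.8 | 14.4% | 22.4% | 28.8% | about 0% |

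These sizes do not depend on the SD or on the number per arm, so they also apply to the smaller caregiver sample.

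**Simulation check** (100 per arm, 4,000 runs per case, null true). The pooled overall arm test rejected in 12.6% to 21.7% of runs with three visits and in 15.7% to 28.5% with four, over ρ from 0.3 to 0.8. The pooled arm-by-time test rejected in at most 1.5%, falling to about 0.2% to 0.3% at ρ = 0.5. With a within-person error term, the arm, time and arm-by-time tests all returned to 4.6% to 5.7%.

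**Power for a 1.5-point difference in change at ρ = 0.5, SD 3.79.**

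- True SE = 3.79 × √(4 × 0.5/100) = 0.535. Power = Φ(1.5/0.535 − 1.96) = Φ(0.84) = 80%.
- Pooled-row SE = 3.79 × √(4/100) = 0.757. Power = Φ((1.5 − 1.96 × 0.757)/0.535) = Φ(0.03) = 51%. An SD of 3.77 gives 52%.
- At ρ = 0.3, 0.7 and 0.8 the correct analysis has 66%, 95% and 99% power. The pooled analysis stays at 51% to 52%.

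**Independent t-tests.** Comparing arms on each person's change score uses one value per person. Its simulated size was 4.8% to 5.9%, so it is valid. An independent t-test of baseline against follow-up within one arm would overstate its SE by 1/√(1 − ρ), or 41% at ρ = 0.5, and its simulated size there was about 0.7%.

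**The case against.** The strongest reply is that the article nowhere says rows are pooled. Its wording could also describe a separate arm comparison at each visit, an ANOVA on change scores, or a repeated-measures ANOVA. Under any of these the error does not arise. Covariance structure is also a detail that an article may leave to an analysis plan.

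This stands in part: pooling is an inference, and the figures above are conditional on it. However, the article goes beyond silence, because it fixes procedures by name. With two arms, an ANOVA run separately at each visit or on each change score has a single contrast, which leaves Tukey HSD nothing to do. The Tukey step has a purpose only if timepoint is a factor, which is also how the sentence describes the analysis. Repeated-measures ANOVA remains possible, but nothing in the text points to it.

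A reader might also infer that the independent t-tests, and with them the primary p-value, are wrong. The documents do not support that. Outcomes defines the primary outcome, and the secondary scales at 3 and 6 months, as differences in change between arms. The univariable phrase about baseline to 3 and 6 months most naturally means the same change scores. An independent t-test is correct for these.

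Finally, the four-visit figures are the extreme case, since Outcomes treats 12 months as a separate long-term follow-up. Even two pooled visits give about 11% at ρ = 0.5.

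**Conclusion.** The point holds for the group-by-timepoint ANOVA/GLM and its Tukey comparisons, and for any independent t-test that might be used for within-arm change. As named, these carry no within-person term.

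If they are run on pooled rows, false positives for the overall arm effect are two to four times the nominal rate at correlation 0.5. With three or four visits the rate is about 13% to 28% over correlations of 0.3 to 0.8. Arm-by-time tests become conservative and lose power.

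The conclusion rests on pooling, which is inferred, on an assumed correlation, and for the power figures on a back-solved SD. The direction holds for any positive correlation. The primary analysis, and the same t-test on 6-month change, are unaffected, so this matters for the secondary results only.

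**What to change.** For each repeated scale, replace the group-by-timepoint ANOVA/GLM and Tukey step with one repeated-measures model. A linear mixed model with unstructured within-person covariance is one suitable choice, and an equivalent GEE is another.

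- Outcomes: the 3- and 6-month values.
- Covariate: the baseline value.
- Fixed effects: arm, visit and arm-by-visit.
- Report: the arm contrast with 95% CI at 3 months and at 6 months.

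Use paired methods for any within-arm change, and say so in the univariable paragraph. Analyse 12 months separately, because control participants will by then have been offered the NP and the contrast no longer compares NP care with none.

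The change needs no new data, only analysis wording and a few lines of SAS or R. Trial status describes the final analysis as still to come, so it can be made beforehand. The price is slightly more analysis work and some secondary p-values that become less favourable.

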### Randomization, allocation, and blinding

This is an interventional study with parallel groups, done through block randomization (variable block sizes) 1:1, using centralized secure website to (1) intervention group (NP-led care) and (2) control group (usual care—community neurologist/family physician and registered nurse (RN), in a non-inferiority framework). The EPICORE Centre will randomize and allocate consented patients who meet eligibility inclusion and exclusion criteria on a 1:1 ratio using a centralized secure website. Block randomization (using variable block sizes) will be used to ensure there are equal participants in the intervention and control arms and to further conceal allocation. The randomization sequence was generated using R blockrand (https://cran.r-project.org/package = blockrand) and the randomization function of REDCap (REDCap Consortium, Vanderbuilt University, Nashville, TN, USA). Participants will be enrolled into the study by the community neurologist’s office (e.g. registered nurse, NP, or neurologist). Participants will register themselves through filling out an iPad questionnaire in the waiting room of community neurologists’ offices, indicating whether they wish to participate in the study or not. The participants, after providing informed consent, will be randomized by the independent EPICORE Centre’s research team to either the intervention group of NP-led care or the control group of standard care provided by community neurologist and registered nurse. After participants have provided informed consent, the EPICORE Centre’s research team will use a centralized website to randomize the patients to either the intervention or control group and then the NP and/or community neurologist will provide the intervention. Participants will be randomized to either the intervention group of NP-led care or the control group of standard care provided by community neurologist and registered nurse. Due to the nature of the intervention, blinding of the providers or patients will not be possible. However, the statistician will be blinded as to which group represents the intervention and control.

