### Sample size and power analysis

Honarmand and Feinstein (2009) [74], validated the use of HADS in PwMS [Baseline scores and standard deviation (SD)]. Using the validation information in the study by Honarmand and Feinstein and the following assumptions of 80% power and a two-sided alpha of 0.05, a total sample size of 200 (100 in each group) will be required to detect 1.5 difference [86], between the intervention and the control groups. The same size has been calculated for both HADS-A and HADS-D. This study will use the sample size calculated for HADS-A, as it required a larger sample size and to ensure there will be sufficient power for both HADS-A and HADS-D. This sample size will be inflated to 220 to account for possible dropouts, losses to follow-up, and withdrawals of consent.

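### The post hoc rule puts Bonferroni on top of Tukey HSD: run over the arm-by-visit cells it corrects the same pairs twice, and with two arms at one visit Tukey does nothing

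*Protocol article*

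**What the plan says.** All of this is in the Protocol article.

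- **Primary test (Statistical analysis).** "The primary outcome of difference in change of HADS-D and HADS-A from baseline to 3 months between the intervention and control" is tested with an independent t-test. Significance is p < 0.05, and no multiplicity adjustment is attached.
- **Other analyses (same section).** Secondary outcomes follow the methods set out further down in that section. These include univariable tests (independent t-tests or non-parametric alternatives) on the 3- and 6-month outcomes, with no adjustment attached. They also include ANOVA and generalized linear models by group and timepoint.
- **Post hoc rule (same section).** The modelling step is followed by: "Post hoc Tukey HSD (Honestly Significant Difference) test will be performed afterwards with adjustments made using the Bonferroni method". Neither the set of comparisons for Tukey nor the Bonferroni divisor is given.
- **Planned effect (Sample size and power analysis).** With "80% power and a two-sided alpha of 0.05", "a total sample size of 200 (100 in each group) will be required to detect 1.5 difference". The SD is not printed; the text points to a cited validation study.
- **Visits and contrasts.** The Data collection section has the patient scales completed at baseline, 3, 6 and 12 months. The Outcomes section defines the comparisons of interest as between-arm differences in change at 3 and 6 months, with a longer-term look at 12 months.

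**The concern.** Tukey HSD and Bonferroni are alternative answers to one question: how to hold the familywise error over a set of comparisons. Tukey's critical value is already set so that the chance of any false positive among all pairs is 5%. Adjusting the same pairs again by Bonferroni makes the rule much stricter than the 5% level the plan sets.

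The sentence follows a model by group and timepoint, so running Tukey over the arm-by-visit cells is a natural reading. Two more faults then appear. Plain Tukey assumes independent cell means, yet the same people supply the means at every visit. It also spends error on pairs that no objective asks about, such as the NP arm at 3 months against usual care at 6 months.

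At stake are the secondary and repeated-measures comparisons. One such contrast could be significant by the unadjusted t-test and non-significant by the post hoc rule, and the section does not say which governs.

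**Working it through.** **Inputs.** From the article: difference 1.5 points, 100 per arm, 80% power, two-sided 0.05, and allocation "on a 1:1 ratio using a centralized secure website". Assumed: the SD, and that the same 1.5 points applies to a post hoc between-arm contrast.

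**1. The plan's own figure.** With n per arm = 2(1.960 + 0.842)² SD²/1.5², a total of 200 cannot be reproduced independently because the SD is missing. Solving backwards gives SD = 1.5 × √(100/2)/2.802 = 3.79 (normal approximation), or about 3.77 for the t-test. SDs of 3.75 to 3.80 return 99 to 101 per arm, so 200 is consistent with an SD in that region.

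**2. Pairs in the Tukey family.** For k cells there are k(k−1)/2 pairs:
- 4 cells (two arms at 3 and 6 months, change scores): 6 pairs
- 6 cells (baseline, 3 and 6 months): 15 pairs
- 8 cells (12 months added): 28 pairs

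**3. Nominal familywise error after both corrections.** This step needs no SD. Bonferroni over the m pairs evaluates Tukey at 0.05/m: 0.05/6 = 0.83%, 0.05/15 = 0.33% and 0.05/28 = 0.18%.

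**4. Critical values and power.** Critical |t| is the studentized-range quantile for k cells divided by √2, with k × 99 degrees of freedom. The noncentrality is 1.5/(3.77 × √(2/100)) = 1.5/0.533 = 2.81. Power is from the noncentral t, treating cells as independent as plain Tukey does.

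| Cells | Critical value, Tukey | Critical value, Tukey + Bonferroni (all pairs) | Power, Tukey | Power, both |
|---|---|---|---|---|
| 4 | 2.58 | 3.19 | 59% | 36% |
| 6 | 2.86 | 3.69 | 48% | 19% |
| 8 | 3.04 | 4.00 | 41% | 12% |

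The unadjusted t-test has critical value 1.97 and power 80%. Bonferroni alone over two between-arm contrasts has critical value 2.26 and power 71%.

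**5. SD range 3.0 to 4.2.** Double-adjusted power runs from 44% down to 12% with 6 cells, from 32% to 7% with 8 cells, and from 64% to 26% with 4 cells.

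**6. A milder divisor.** If Tukey covers all cells but Bonferroni divides only by 2, power at SD 3.77 is 49%, 39% and 33% for 4, 6 and 8 cells.

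**7. The within-visit reading.** With two cells Tukey's critical value is 1.97, identical to the t-test. Bonferroni over 2, 3 or 4 visits then leaves about 71%, 65% or 61%. There is no double correction.

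**8. Where the loss comes from.** With 6 cells, Tukey alone takes power from 80% to 48% (32 points) and Bonferroni takes it on to 19% (29 points). About half the loss is due to the all-cells family rather than to the second correction.

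**9. Repeated measures.** A between-arm contrast at one visit compares different people, so independence is reasonable for that pair. It fails for within-arm pairs across visits, and hence for the joint distribution behind Tukey's critical value.

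**The case against.** The strongest reply is that the rule does not reach the comparison the trial was sized for. That stands. The 1.5-point effect is the 3-month primary contrast, tested by an unadjusted t-test with about 80% power. A reader might infer that the planned effect would usually be declared non-significant; the article does not support that.

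A reader might also infer that a true 6-month effect on HADS, MFIS or EQ5D would be reported as absent. That does not follow either. The same section provides unadjusted t-tests for those outcomes, so the most that can be said is that two results may conflict. No SD or effect size is given for MFIS or EQ5D, so the HADS figures cannot be carried over to them. Nor can it be said that confidence intervals would be too wide, since the section plans none.

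The comparison family is unstated, and an SAP that is not shown may name it. On the within-visit reading power stays at 61% to 71%. This makes the size of the loss conditional. It does not rescue the sentence, because on that reading naming Tukey adds nothing.

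Finally, the error is conservative: it adds no false positives. That is true, and it limits the seriousness of the point.

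**Conclusion.** The point holds as a defect of the post hoc step. Over arm-by-visit cells the stated rule corrects the same pairs twice, with a nominal familywise error of 0.83%, 0.33% or 0.18% (4, 6 or 8 cells) instead of 5%. Within a visit, the Tukey step is empty. Neither reading gives the rule as written a clear purpose.

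The power figures are illustrations. They rest on the back-solved SD, a 1.5-point contrast, 100 per cell and Bonferroni over all pairs. On those terms double-adjusted power is below 50% in all three layouts. That remains so across SD 3.0 to 4.2 with 6 or 8 cells, but not with 4 cells, where it reaches 64% at SD 3.0. The primary conclusion is unaffected. Dropping Bonferroni alone would not restore power in the 6- or 8-cell family; the family has to be narrowed as well.

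**What to change.** 1. Delete the Tukey-plus-Bonferroni sentence.
2. For each repeated scale, fit a model that accounts for repeated measures on the same person, and report only the between-arm contrasts in change at 3 and 6 months.
3. If adjustment is wanted, name one method (Holm or Bonferroni) and list the contrasts it covers.
4. State that the primary 3-month t-tests lie outside that family, and which analysis governs each secondary contrast.

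The cost is a few sentences in the analysis section or the SAP, with no extra data or participants. The Trial status section places the final analysis still ahead, so the change should be dated and made before the statistician is unblinded.
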